## Abstract

**Background:**

Transcutaneous auricular vagus nerve stimulation (taVNS) has recently been explored for the treatment of Disorders of consciousness (DoC) caused by traumatic brain injury. The evidence of taVNS during the consciousness recovery has been recently reported. However, the mechanism of taVNS in the recovery of consciousness is not clear. This study attempts to investigate the effectiveness of taVNS in DoC by means of Coma Recovery Scale-Revised (CRS-R), Magnetic resonance imaging (MRI), Electrophysiology (EEG), and Single-molecular array (Simoa).

**Methods/design:**

Nighty patients with DoC acquired brain injury are randomized into one of three groups receiving sham taVNS or active taVNS (just left and left or right), respectively. Each of the three groups will experience a 40 days cycle (every 10 days for a small period, baseline 2 weeks, intervention 2 weeks, 40 min per day, 5 days per week, then no intervention for 2 weeks, intervention 2 weeks, 40 min per day, and 5 days per week). Primary outcomes (CRS-R) will be recorded five times during every period. Secondary outcomes will be recorded at the first and at the last period [MRI, EEG, Phosphorylated tau (P-tau), and Neurofilament light chain (NFL)]. We will take notes the adverse events and untoward effects during all cycles.

**Discussion:**

Transcutaneous auricular vagus nerve stimulation as a painless, non-invasive, easily applied, and effective therapy was applied for treatment of patients with depression and epilepsy several decades ago. Recent progress showed that taVNS has behavioral effects in the consciousness recovery. However, there is no clinical evidence to support the effects of taVNS on brain activity. Therefore, we will design a randomized controlled trial to evaluate the effectiveness and safety of taVNS therapy for DoC, and explore neural anatomy correlated to taVNS during the consciousness recovery. Finally, this protocol also tests some biomarkers along with the recovery of consciousness.

**Clinical Trial Registration:**

Chinese Clinical Trial Registry, ChiCTR2100045161. Registered on 9 April 2021.

## Introduction

1.

Acquired brain injury is often known as a “silent epidemic disease,” which is a general term for all brain injuries (1, 2). Acquired brain injury includes infection, hypoxia, and trauma, which can cause systemic or focal injury, and a series of pathophysiological changes (such as brain hematoma, brain contusion, and diffuse axonal injury). There are about 1.7 million Traumatic brain injury (TBI) events occur every year in the United States (3). But in China, there are no accurate epidemiological investigation data. The survival rate of Disorders of consciousness (DoC) patients after severe brain injury has been significantly increased due to advanced medical treatment and healthcare (4). However, it caused the heavy economic burden and great mental stress for family members. Currently, early assessment and health management of DoC are facing a great challenge because of its unclear pathophysiological nature. Understanding the biological basis of DoC would have important implication for the development of diagnostic and therapeutic strategies.

Dysfunction of the brain in certain areas, combined with the disruption of the neural connections between and within neural networks, can lead to DoC (4). DoC patients are in coma kept closed eyes, lack of arousal, and awareness (5), and do not respond to environment. Unresponsive wakefulness syndrome (UWS) of DoC (previously called Vegetative State, *VS*) is defined by some intermittent spontaneous arousal observed after tactile, auditory, or painful stimulation (1), but these DoC patients in no self-consciousness cannot consciously interact with their surrounding environment (6). Minimally consciousness state (MCS) patients have arousal and the ability to consciously interact with the environment, such as visual tracking, object localization; reaching, or instruction following (6). These changes are unstable but reproducible. MCS can be further divided into minus (MCS−) or plus (MCS+) (7). While consciousness is fluctuating in MCS, it is still possible to have the residual consciousness behavior can be monitored by careful assessment.

To date, there is no single effective way to predict, evaluate, and intervene in early severe brain injury (2), Therefore, exploring accurate assessment methods and effective intervention strategies for DoC are urgently required in this emerging fields. Transcutaneous auricular vagus nerve stimulation (taVNS) is a potential intervention in treatment of DoC. Certain visceral representative areas of the ear region produce brainstem-to-central neural modulation effects similar to invasive vagus and neural stimulation (8, 9). Because taVNS is non-invasive and has no need for surgical condition (8, 9), low cost and easy to perform for DoC patients in families or communities. It has been shown that taVNS can produce a beneficial effect in DoC (4), but the underlying mechanism is unclear.

The auricular branch of the vagus nerve is the source of sensory information to the ear. The external ear’s central area contains sensory fibers, which are situated close to the Cymba Concha section of the auricle. The auricular vagus nerve’s afferent neurons go to the inferior vagal ganglion, and then the impulse is sent to the solitary tract nucleus in the brainstem. The solitary tract is the primary receptor of sensory information from different branches of the vagus nerve, which then sends out various signals to other parts of the body, such as the locus coeruleus. This area of the reticular activating system is a major source of adrenaline-inducing projections that reach the cortex, subcortex, and brainstem. It appears that the activation of the locus coeruleus may be the cause of many of the observed therapeutic outcomes from VNS and taVNS (10). The firing of neurons in the locus coeruleus causes a massive release of norepinephrine in the thalamus and hippocampus, which is an essential part of the noradrenergic pathway and is crucial for alertness, arousal, and the fight-or-flight reaction (11). The vagus nerve in humans stimulates metabolic processes in the forebrain, thalamus, and reticular formation, and it also regulates activity in the brainstem, as well as the nucleus of the solitary tract (NTS), dorsal raphe nuclei, amygdala, and hippocampus (11).

Based on our current understanding of taVNS related to the awareness-related neural pathways, vagal cortical pathway model has been proposed (4). The vagal cortical pathway model through six distinct strategies to influence brain activity and consciousness: boosting the excitability of the ascending reticular activating system, activating the thalamus, reconstructing the cortical striatal-thalamic-cortical network, establishing negative connections between external and default mode networks by stimulating salience networks, stimulating the norepinephrine pathway to raise external network activity and connectivity, and raising excitability within the default mode network through the serotonin pathway (4). This model was constructed to investigate the mechanism of action that taVNS exerts neural modulatory effects as therapeutic intervention in the management of DoC. Therefore, the vagal cortical pathway model should be demonstrated in prospective randomized controlled clinical trials. This current study, with its randomly chosen participants, seeks to (1) gauge the effectiveness of taVNS in DoC; (2) confirm or refute vagal cortical pathway model (10, 12, 13); and (3) identify biomarkers for diagnosis and targets for therapeutic intervention (2).

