#### Magnetic resonance imaging

2.12.2.

In this study, rest Fmri research must always include a brainstem assessment in order to verify the Vagal Cortical Pathways model’s pathways. This can be confidently relied upon as a guarantee of quality in taVNS studies, as it clearly demonstrates the stimulation of the vagus nerve (4). Furthermore, subcortical regions like the thalamus and striatum should be taken into account. Brain connectivity can be estimated by utilizing the thalamus, frontal lateral cortex, anterior cingulate cortex, insula, and posterior cingulate cortex as seed regions in Fmri studies. Moreover, measuring brain activity during tasks should be the preferred approach (21, 22). In severe TBI, an increase in fractional anisotropy (FA) on the initial postinjury diffusion tensor imaging (DTI) was associated with a favorable outcome, and these results suggest that it is secondary to axonal regrowth during later recovery. A variety of other cognitive and functional outcomes in mild to severe TBI have been correlated to DTI (23). Finally, DTI-FA should be analyzed in our study (More MRI details are shown in Supplementary material).

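### Aim 2 promises to confirm or refute a six-route model, but the measures cannot attribute two routes to their transmitters, so the whole model cannot be confirmed; support should rest on active versus sham

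*Protocol article*

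**What the plan says.** The Introduction describes the model as a set of six mechanisms: "The vagal cortical pathway model through six distinct strategies to influence brain activity and consciousness". The fifth is "stimulating the norepinephrine pathway to raise external network activity and connectivity" and the sixth is "raising excitability within the default mode network through the serotonin pathway". The second aim is then to "confirm or refute vagal cortical pathway model".

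The secondary outcomes in section 2.10 are EEG, MRI, P-tau and NFL. Section 2.12.1 says the EEG analysis will be mostly spectral power. Section 2.12.2 specifies resting fMRI with a brainstem assessment meant to verify the model's pathways, adds the thalamus and striatum, names five seed regions for connectivity, and adds DTI-FA. It says of the brainstem assessment: "as it clearly demonstrates the stimulation of the vagus nerve". Section 2.13 names two comparisons, pre-post and active against sham, without saying which one bears on the model.

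On scan timing the abstract says: "Secondary outcomes will be recorded at the first and at the last period". Sections 2.1 and 2.10 give different times, compared below.

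**The concern.** An aim to confirm or refute a model obliges the trial to measure what sets the model apart from its rivals. Routes 5 and 6 are set apart by the transmitter said to carry the effect, and no listed measure observes a transmitter. A change in the external or default mode network would fit those routes, but it would equally fit any other cause of the same change.

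The second problem is the choice of comparison. These patients may recover for reasons unrelated to stimulation, and connectivity may change with recovery. If a pre-post change in the active arms may count as evidence for the model, ordinary recovery could be reported as confirmation. At stake is the mechanistic conclusion drawn from one of the three stated aims.

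**Working it through.** The plan gives no figure on this point. Its one calculation, the CRS-R sample size, does not bear on it. The check is to set the six routes beside the listed measures. The article does not say which seed belongs to which network, so the pairing below is an assumption.

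| Route in the Introduction | Related measure in 2.12.2 | Transmitter named in the route | Transmitter measured |
|---|---|---|---|
| 1 Ascending reticular activating system | Brainstem assessment | none | not needed |
| 2 Thalamus | Thalamus | none | not needed |
| 3 Cortico-striato-thalamic network | Striatum, thalamus, frontal lateral cortex | none | not needed |
| 4 Salience network acting on the external and default mode networks | Insula, anterior cingulate, with the external and default mode seeds | none | not needed |
| 5 External network | Frontal lateral cortex | norepinephrine | no |
| 6 Default mode network | Posterior cingulate | serotonin | no |

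**Count.** Routes with no related measure: 0 of 6. Routes whose defining transmitter is not measured: 2 of 6, or 33%. The second figure counts missing attributions, not unmeasured routes.

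**What follows for confirmation and refutation.** Confirming the whole model needs all six routes, including the transmitter step in two of them, and that step is not observed. A component can be contradicted: if active and sham differ little in change at a region where the model predicts a difference, and the estimate is precise enough to say so, that counts against the prediction. Confirmation of the whole is out of reach; evidence for or against parts is not.

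**Comparison.** A pre-post change in an active arm contains any effect of stimulation plus the change that would have happened anyway. The active-minus-sham difference in change removes the second part in expectation, because allocation is random. Section 2.13 permits both comparisons, and only the second bears on the model.

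**Scan timing.** The abstract gives four periods of 10 days in the order baseline, intervention, no intervention, intervention, so the fourth period ends at 4 × 10 = 40 days.

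| Place | Scan times | Consequence |
|---|---|---|
| Abstract | First and last period | Pre-treatment scan exists |
| 2.1 | Beginning and end of the fourth period | Read literally, both scans follow the first intervention block, so there is no pre-treatment scan |
| 2.10 | Baseline and end of the fourth week, 4 × 7 = 28 days | Pre-treatment scan exists, but the last scan precedes the second intervention block |

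Day 28 falls in the third 10-day period (days 21 to 30). On the two-week blocks that the abstract also gives, the end of week four is the end of the first intervention block. Either way the second block is not covered. Section 2.6 adds MRI and EEG at follow-up for eligible subjects, which does not settle the earlier times.

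**The vagal stimulation statement.** The scan times in the article are visits. A difference between resting scans at two visits shows a change in state between them; by itself it does not show that the vagus nerve was stimulated.

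**The case against.** The strongest reply is that the design is better than a sceptic would allow. The trial has a randomised sham arm, section 2.13 plans active against sham, and the MRI and EEG data are among the outcomes to be tested. That controls for spontaneous recovery and allows evidence for or against each component. This stands.

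A reader might therefore go too far in several ways:

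- **That the design can neither confirm nor refute anything.** The documents do not support this, because the randomised imaging comparison can support or contradict the model's anatomical and network predictions.
- **That two routes are not measured at all.** Their network endpoints fall within the planned connectivity analysis. The Introduction also links norepinephrine release to the locus coeruleus and lists the raphe nuclei among vagal targets, so the brainstem assessment may touch both. Even so, connectivity from such a nucleus is not a measure of its transmitter, and the attribution stays untested.
- **That the plan lacks a scan during stimulation, or a result that would refute the model.** The article sends MRI detail to a supplement that is not shown. Such items may be there, and their absence from a condensed article is not a finding.
- **That the imaging paradigm is undecided,** because section 2.12.2 also says "measuring brain activity during tasks should be the preferred approach". The section states resting fMRI for this study, the task remark reads as general comment with citations, and no task is scheduled.

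It can also be said that the scan-time sentence in 2.1 may mean the start of the study and the end of the fourth period. That is possible and would agree with the abstract, but it is not what the sentence says, and 2.10 would still differ.

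**Conclusion.** The point holds in limited form. Aim 2 is wider than the listed measures: the transmitter attribution in 2 of 6 routes is not tested, so the model as a whole cannot be confirmed, whatever the imaging shows. The brainstem, thalamic, striatal and network predictions, including the external and default mode networks, remain testable by active against sham. Leaving the pre-post comparison available as evidence for the model invites a conclusion that recovery alone could produce. The conflict over scan times matters as much: on a literal reading of 2.1, change from before treatment could not be estimated at all.

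This rests on the measures listed in the article being complete as to kind, that is, on the supplement adding no norepinephrine or serotonin measure. The matter concerns a secondary, mechanistic aim. It leaves the CRS-R primary outcome untouched, but it should be corrected because it decides what the trial may conclude about mechanism.

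**What to change.** 1. Restate aim 2 as exploring whether active taVNS, compared with sham, changes imaging measures in the model's brainstem, thalamic, cortico-striatal and network components, including the external and default mode networks. State that the norepinephrine and serotonin attribution in routes 5 and 6 is not tested.
2. In 2.13, say that support for a component comes only from an active-versus-sham difference in change at the regions named in 2.12.2 (brainstem, thalamus, striatum and the cortical seeds). Pre-post change in the active arms may be described but does not count as support.
3. Do not carry the 2.12.2 statement that the scan demonstrates vagal stimulation into the conclusions from between-visit resting scans.
4. Reconcile the scan times in the abstract, 2.1 and 2.10, and make plain whether a pre-treatment scan exists for every patient.

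Items 1 to 3 change wording only and add no procedure. Item 4 is also wording if the conduct of the trial is already uniform; if it is not, the scan times actually used must be reported. The cost is a more modest mechanistic claim.

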## Methods

2.

### Study design

2.1.

Ninety patients suffering from DoC will be chosen for this prospective, randomized trial which involves double-blinded assessments. The participants will be randomly divided into the intervention and control groups with an even distribution. The control group will be administered ear lobe therapy, in contrast to the intervention group which will receive the active taVNS. We will stimulate left cymba conchae for one group, the second group subjects will be stimulated left cymba 20 min and right cymba 20 min once a day. Because we have not seen the side effects from the clinical practice, and the right vagus nerves modulate the left hemisphere. This study will last 40 days and a half-year observation period will follow. CRS-R behavioral improvement will be monitored five times every 10 days. At the beginning and the end of the fourth period, the following tests will be carried out: EEG, MRI, and measurement of certain biomarkers related to brain injuries. All side effects during each treatment will be documented. This study will be implemented in Shanghai Yongci Hospital, and rehabilitation therapists are held accountable for following the standard operating procedure and evaluating the trial’s progress at all clinical sites. This trial is illustrated in Figure 1.

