### Trail protocol

2.5.

Ninety patients will undergo two sessions 10 days apart, with CRS-R and EEG performed before and after VNS. The active session will stimulate the left or right cymba conchae and inner tragus (TENS-200A, SN number: E200A16A000144, the B mode type; stimulation parameters: output pulse width degree of 200us, 20 Hz output 7 s, 4 Hz output, and 3 s alternate cycle output). The taVNS stimulator will be monitored according to patients’ response. The sham stimulation will be applied over the earlobe. We expect behavioral and EEG metrics to be improved in a majority of patients (See Figure 2).

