### Outcome measures

2.10.

The primary outcome for this study, coma recovery as measured by the Coma Recovery Scale-Revised (CRS-R), will be assessed at five time points for each period, ranging from the first to the fourth. This data will be used to determine the efficacy of the intervention being studied. The secondary outcomes of this study will be measured at both the baseline and the end of the fourth week of the study. Specifically, EEG, MRI, P-tau, and NFL will be used to measure these outcomes. These measurements will provide valuable insight into the effects of the study and help to further understand the results. Any detrimental outcomes or side effects will be noted during the course of the treatment.

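### The timing of EEG, MRI, p-tau and NFL is stated in conflicting ways that, read literally, estimate the effect of different parts of the treatment

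*Protocol article*

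**What the plan says.** The Abstract (Methods/design) sets the frame: "Each of the three groups will experience a 40 days cycle". It divides this as "every 10 days for a small period, baseline 2 weeks, intervention 2 weeks, 40 min per day, 5 days per week", and continues "then no intervention for 2 weeks, intervention 2 weeks, 40 min per day, and 5 days per week". The order is therefore baseline, first course, break, second course.

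The secondary outcomes are then timed in several places:

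- Abstract, Methods/design: "Secondary outcomes will be recorded at the first and at the last period".
- Study design (2.1): "At the beginning and the end of the fourth period, the following tests will be carried out: EEG, MRI, and measurement of certain biomarkers".
- Outcome measures (2.10): "measured at both the baseline and the end of the fourth week of the study", followed by "Specifically, EEG, MRI, P-tau, and NFL will be used to measure these outcomes".
- Trail protocol (2.5), for EEG: "Ninety patients will undergo two sessions 10 days apart, with CRS-R and EEG performed before and after VNS".
- Single-molecule Array (2.12.3): blood is drawn once ahead of the stimulation and once following it, with no day given.

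Statistical analysis (2.13) plans pre versus post and treatment versus sham comparisons and includes MRI and EEG among the outcomes tested.

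**The concern.** In a pre-post design the two measurement times define what is estimated. If the first value is taken at the start of period 4, it follows randomisation and a complete course of stimulation. Any effect of that course that persists is then subtracted from the measured change. If the last value is taken at the end of week 4, the second course is not observed at all.

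Two of the three aims in the Introduction depend on these measurements: testing the vagal cortical pathway model and identifying biomarkers. Conflicting text also carries two practical risks. Patients may be measured at different points, or the contrast may be settled after the data are known.

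**Working it through.** **Inputs.** A 40-day cycle; four phases, each described both as 10 days and as 2 weeks; 5 sessions per week in the stimulation phases (all from the Abstract). Study design also gives 40 days.

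**The plan's own figure.** 4 periods × 10 days = 40 days, which reproduces the stated cycle. Alternatively, 4 phases × 2 weeks = 8 weeks, which is 8 × 5 = 40 weekdays but 8 × 7 = 56 calendar days. Both calendars can be read from the text, so both are used below.

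**Planned treatment, 2-week calendar.** Each course is 2 weeks × 5 days = 10 sessions, so two courses are 20 sessions. On the 10-day calendar the share of stimulation days is used instead.

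**Phases.**

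| Phase | 10-day calendar | 2-week calendar |
|---|---|---|
| 1 Baseline | days 1–10 | days 1–14 |
| 2 First course | days 11–20 | days 15–28 |
| 3 No stimulation | days 21–30 | days 29–42 |
| 4 Second course | days 31–40 | days 43–56 |

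**Treatment given by each stated time.**

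| Time | 10-day calendar | 2-week calendar |
|---|---|---|
| End of phase 1 | day 10: 0% | day 14: 0 of 20 |
| End of week 4 (2.10, last value) | day 28, in the break: 50% | day 28, end of first course: 10 of 20 |
| Start of period 4 (2.1, first value) | after day 30: 50% | after day 42: 10 of 20 |
| End of period 4 (2.1, last value) | day 40: 100% | day 56: 20 of 20 |

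**Gap between the two final times.** 40 − 28 = 12 days, or 56 − 28 = 28 days. On either calendar the whole second course lies between them.

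**Contrast estimated under each text, read literally.**

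- Abstract: from 0% to as much as 100% of treatment. It covers both courses if the last-period value is taken at the end of that period; the Abstract does not give the day.
- Study design: from 50% to 100%, the second course only.
- Outcome measures: from 0% to 50%, the first course only.

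The EEG wording in Trail protocol cannot be placed with certainty. The 10 days may separate two individual sessions or describe the break between two courses. Either way, it does not say around which stimulation the recordings are made.

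**The case against.** The best defence is that these are slips of language. The sentence in Study design never uses the word baseline, and it could be read as the start of the study and the end of the fourth period. That would agree with the Abstract and with the blood sampling in 2.12.3. Likewise, week in Outcome measures may stand for period. Figures 1 and 2 are not available here and may show a clear schedule.

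This has weight, and it rules out the claim that the plan deliberately sets a post-treatment baseline. A reader might infer that from 2.1, but the text supports it only on the literal grammar, where both nouns attach to the fourth period. It does not remove the contradiction. Reading 2.1 loosely leaves the fourth week in 2.10 in conflict with the other two texts. Full agreement needs two separate corrections that the article does not make, and the EEG wording in 2.5 would still be open. A figure could show the intended schedule but would not make the present text consistent.

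Two further inferences are tempting and fail:

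- A reader might attach a loss of power to the shortened contrast. The documents give 90% power only for CRS-R (Sample size, 2.3) and none for these outcomes. How the effect divides between the courses is also unknown, so no power figure applies.
- A reader might say that a week-4 value could not be related to behaviour. CRS-R is recorded five times in every period, so it could be paired with CRS-R from about the same time. The result would describe the first course only, which is a different question but an interpretable one.

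**Conclusion.** The concern holds as an internal contradiction about when the secondary outcomes are measured. Taken literally, the texts estimate the effect of both courses, of the second course alone, or of the first course alone. The end of week 4 falls at half of the planned treatment on either calendar, and the two stated final times differ by 12 to 28 days and by the entire second course.

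This rests on the phase order in the Abstract and on literal wording. The second-course-only reading of Study design lapses if its beginning means the start of the study; the conflict with Outcome measures does not. The point should be fixed, but it ranks below a fault in the primary analysis, because it touches secondary outcomes and leaves the CRS-R comparison as it is. The documents do not show which schedule was followed in practice.

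**What to change.** Reconcile the Abstract, Study design (2.1), Trail protocol (2.5) and Outcome measures (2.10) to one schedule for EEG, MRI, p-tau and NFL: one measurement in period 1 before the first stimulation and one at the end of period 4. This agrees with the Abstract and with the sampling on either side of the intervention in 2.12.3, and it spans both courses. Give the times as study days, so that it is clear whether a period is 10 days or 2 weeks.

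Because enrolment started in April 2021 (Trial status), also state the schedule actually used, flag each measurement taken at another time, and do not analyse any value obtained after the first course as pre-treatment.

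The number of measurements stays at two per patient. If practice already matched this schedule, the cost is wording in four places. If it did not, the cost also includes classifying the existing scans and samples by actual date and reporting which contrast they support.
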